## 7 ELIGIBILITY CRITERIA

### 7.1 Inclusion criteria

TreatPaCS includes preschool age children

- who stutter (identified with the Stuttering Severity Instrument-4 (SSI-4) or the Test For Stuttering Severity-Non Readers, available in Dutch and French (TVS-NL/TSB-NL))
- who are aged between 2 - 6.5 years
- who have no hearing loss, reported by the parent(s)
- who have, if bilingual, a parent who speaks a language that the SLT understands and speaks to allow clear communication
- who have at least one parent agreeing to be intensively involved in treatment and knowing that s/he will implement the treatment at home
- who have at least one parent who is willing and able to video record his/her child regularly

A PCWS can participate in the trial if the Informed Consent Form is signed by one of the parents.

### 7.2 Exclusion criteria

TreatPaCS will not include preschool age children with a syndrome such as Down Syndrome.

*Note: PCWS with comorbidities (Autism Spectrum Disorder, ADHD, language disorders, ...) are not excluded from the trial as the goal is to resemble standard of care.*

## 8 TRIAL PROCEDURES

### 8.1 Recruitment

#### 8.1.1 Patient identification

The participating SLT will recruit the PCWS when the parent contacts the SLT's private practice. The participating SLT will notify colleague SLTs in the neighbourhood about TreatPaCS and will propose them to refer PCWS to her/his private practice.

#### 8.1.2 Screening

In the first intake session (=screening), the participating SLT

- identifies the stuttering in the PCWS (with the measuring instrument SSI-4 or TVS-NL/TSB-NL).

- collects information from the parent about the PCWS, his/her stuttering and about the parent with the Anamnesis form (Appendix 3). The SLT records this in the PCWS' speech-language therapy file (on paper or electronically).
- educates the parents about stuttering to decrease the level of concern.
- decides, based on the age of the PCWS, the severity of the stuttering, the family history of the stuttering and the evolution of stuttering since onset, which action needs to be taken:
  - (1) install a period of active monitoring of maximum 3 months to evaluate the progress of the stuttering (if signs of natural recovery are present),
  - (2) initiate stuttering treatment or
  - (3) not initiate stuttering treatment.

If a period of active monitoring is installed, the SLT decides when sessions are scheduled (often every 4 or 6 weeks, depending on the need of the PCWS and the parents). The SLT decides how the parents record information about the stuttering (qualitative information by keeping a diary or quantitative data by recording daily typical stuttering severity scores on a 10-point scale with 0 = no stuttering, 1 = extremely mild stuttering and 9 = extremely severe stuttering). If the situation requires it, the SLT may provide advice, for example taking turns in conversations or not interrupting the PCWS when s/he is talking. The SLT does not model treatment techniques or introduces no techniques that require clinical follow-up. The SLT-file will provide an overview of advice that could be given during the active monitoring. The SLT decides based on the context of the PCWS and family if and when to initiate stuttering treatment.

If stuttering treatment needs to be installed, the next session is the baseline session.

If no stuttering treatment is initiated, the PCWS is not invited to participate in TreatPaCS.

- screens the PCWS and family for the inclusion and exclusion criteria.
- provides the parents with an information letter and consent form for TreatPaCS and asks consent of at least one of the parents (see 8.2 Consent). The signed consent form needs to be returned to the SLT at least 24 hours before the baseline session so that the PCWS is randomised before the start of the baseline session. The questionnaires need to be completed by the parent before the baseline session.

## 8.2 Consent

The participating SLT provides the parent(s) of the PCWS (who was successfully screened for eligibility) with an information letter and consent form. At least one of the parents signs the informed consent form. If the PCWS's parents are divorced, the SLT may consider it necessary to obtain both parents' signatures.

The sponsor's procedure regarding signing the informed consent form for minors in research studies requires that one of the parents signs the informed consent form. To increase understanding, a summary of the consent form with the most important points will be provided.

The participating SLT

- discusses with the parent the nature, objectives and possible risks of the TreatPaCS trial
- informs parents that the treatment approaches are delivered as standard of care treatment. Hence, they will have no extra costs. They will be asked to video record their child and answer some questionnaires at 7 points within 2 years and once after 5 years post-randomisation. For the first 7 times, parents will receive a voucher to compensate for the extra work because it is asked within the four-year period in which the study is funded.
- provides the opportunity to the parent(s) to ask questions
- assesses the parent's capacity to give his/her consent. The parent understands the purpose and nature of the trial, what research involves, the benefits of the trial, the risks and the burdens. The parent also understands what the alternative is to taking part. The parent is given sufficient time to make the decision and knows that it is a free choice.

The parent is asked to inform the participating SLT if s/he wants to participate in the TreatPaCS trial before the baseline session and to video record a speech sample of 10 to 15 minutes from a home situation before the next session. Clear instruction for how to record the video will be provided.

Parents know that the treatment will be standard of care.

An information form for the PCWS is also provided. The SLT informs the PCWS about the study by reading aloud what will happen at the child's language level and signs the form. This happens during the baseline session.

## 8.3 Trial randomisation

Stratified randomisation will be used according to site (30 sites) and gender. We will use a minimisation procedure to randomize. Minimisation assures similar distribution of selected participant factors between study groups. The first participant is truly randomly allocated; for each subsequent participant the imbalance score is computed based on all previous allocations as well as the hypothetical allocation of the current participant to each

treatment. The preferred treatment is then selected by choosing the treatment allocation associated with the smallest imbalance score.

The distance measure used to calculate the imbalance score is marginal balance. Marginal balance computes the cumulative difference between every possible pair of level counts (i.e. the number of participants in that particular factor level).

The allocation of the new participant is then made at random with a heavy weighting in favour of the intervention that would minimise imbalance. The remaining probability is equally divided between the non-preferred treatments. Full details will be provided in a separate document with restricted access.

If siblings or twins are eligible for this trial, only one child participate in the study otherwise there will be a dependency in the data. It is not feasible for a parent to implement two different treatment approaches. To avoid confusion, the second PCWS will receive the same treatment approach but will not be included in the study.

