| Internal reference             | TreatPaCS                                                                                                                                                                                                                                                                                                                                                                                                                                                                                                                                                                                                                                                                                                                                                                                                                                                                                                                                                                                                                                                                                      |
| Trial Design                   | A three arm 1:1:1 randomised, open-label non-inferiority parallel group pragmatic trial                                                                                                                                                                                                                                                                                                                                                                                                                                                                                                                                                                                                                                                                                                                                                                                                                                                                                                                                                                                                        |

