## **6 STUDY SETTING**

TreatPaCS is a trial with 30 sites (SLTs). Eligibility criteria for the sites and participating SLTs are:

- The site is a private practice specialised in stuttering (does not need to be exclusively in stuttering)
- The participating SLT is experienced in treating PCWS with at least 2 years of experience
- The participating SLT is prepared to deliver the three treatment approaches
- The participating SLT attends (again) the three workshops (Mini-KIDS, SCBT and LP) and the International Conference on Harmonisation of technical requirements for registration of pharmaceuticals for human use- Good Clinical Practice (ICH-GCP) workshop
- The participating SLT starts stuttering treatment with at least 1 PCWS per three months or more (based on a retrospective survey conducted during the feasibility phase of the study)

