## **8.4 Blinding**

The participating SLTs, PCWS and their parents are not blinded to the treatment approaches that they deliver/receive. The three treatment approaches (Mini-KIDS, SCBT and the LP) use distinct techniques. Blinding is thus impossible.

The video analysts who are scoring %SS and SR are blinded to the treatment approaches that the PCWS receives. In the unlikely event that a video analyst is unblinded for the treatment that is delivered by the SLT in a video, for example if the video analyst recognises the name of a PCWS in the video because it was mentioned by the SLT during a SLT-RCT committee meeting, the video analyst will stop rating the video and will transfer the video to another video analyst who is blinded to the treatment.

Two video analysts are not blinded and will assess the French and Dutch video recordings for treatment fidelity.

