## 14.3 Public and Patient Involvement

### 14.3.1 Design of the research

A focus group was held to discuss the design of the study with six SLTs. During this focus group, the initial, general set-up was described. They formulated (1) doubts:

*“What if the treatment program does not provide the desired results. Will parents “blame” the outcome on being in the study?” - “It is a challenge not being able to follow your personal preference as stuttering specialist.” - “What if not enough children can be recruited...”*

(2) and positive reflections:

*“It is positive that the study does not include a control group consisting of children who don’t receive treatment.”*

*“The study may help making the choice between treatment programs in the future more easily.” - “Expertise in treating stuttering with the [different] programs may have an impact on the study. It is great that workshops and guidance for the treatment programs are provided.”*

Parents of PCWS and were receiving treatment with Mini-KIDS (N = 3) at the time they were interviewed, with one parent who stuttered himself, formulated that

*“A timely, profound approach for PCWS is essential. Great that researchers want to investigate that.” - “I think that is a great idea. It is only positive to timely intervene to avoid problems in the long run. If this can help to support parents and children who stutter, I can only be in favour of the idea.” - “Being able to offer several treatment programs enables adequate support for young children who stutter. Choosing the adequate treatment program will help to shorten the treatment period.”*

To redefine the primary outcome based on the suggestions from the Trial Board, two parents of PCWS (one who received treatment with the LP and one with Mini-KIDS) were contacted and asked for their opinion.

The patient representatives will review the final draft version of the protocol and provide the TreatPaCS’ team with their feedback. Modification may be done based on their feedback.

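### Minimising on 30 single-therapist sites with heavy weighting makes the next arm partly predictable to the unblinded recruiter, and the protocol has no check for it

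*Protocol*

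**What the plan says.** The Trial Summary describes the design as "A three arm 1:1:1 randomised, open-label non-inferiority parallel group pragmatic trial". Section 8.3 gives the allocation factors: "Stratified randomisation will be used according to site (30 sites) and gender". The method is minimisation on marginal balance with a random element: "The allocation of the new participant is then made at random with a heavy weighting in favour of the intervention that would minimise imbalance". The rest of the probability is shared equally by the other two arms, and the details, including the weight, are kept in a restricted document.

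Section 6 equates sites with therapists ("TreatPaCS is a trial with 30 sites (SLTs") and makes it a condition that "The participating SLT is prepared to deliver the three treatment approaches". Section 8.4 adds: "The participating SLTs, PCWS and their parents are not blinded to the treatment approaches that they deliver/receive".

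The SLT recruits (8.1.1), screens (8.1.2), takes consent (8.2) and files the randomisation request (8.3.1). On starting treatment, 8.1.2 says: "The SLT decides based on the context of the PCWS and family if and when to initiate stuttering treatment". One option there is up to 3 months of active monitoring. Section 14.3.1 records this remark from the SLT focus group: "It is a challenge not being able to follow your personal preference as stuttering specialist".

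There are safeguards. Trial-centre staff make the allocation centrally (8.3.1), and the arm is revealed only after the baseline questionnaires, KiddyCAT and videos are in (8.7.1). The primary model in 11.3.2 has program as its only predictor. Baseline variables enter it only through the adherence weights.

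**The concern.** Minimising on site pulls each site's three arm counts together. The person who sees those counts is the one who decides whom to put forward and when. The guess does not need the undisclosed weight, because the site's own list of past allocations is enough. Central allocation, late reveal and a restricted document hide the current assignment, but none of them hides that list. No section of the protocol mentions predictability.

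In an open trial, concealment of the next arm is the main protection against selective enrolment. If children with a better outlook were put forward when one arm was expected, the 18-month difference in %SS would carry that selection. Neither the intention-to-treat nor the per-protocol analysis would remove it, because it acts before randomisation. The adherence weights address non-adherence, not who was enrolled.

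**Working it through.** **Inputs from the protocol.** Margin 1.0 %SS, SD 1.7, one-sided alpha 1.25%, power 90%, 73 evaluable per arm, 11% dropout, 249 children (11.1). 30 sites (6, 8.3). Marginal balance summed over pairs of arm counts, remainder split equally (8.3).

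**Assumptions.** Probability of the preferred arm 0.8, range 0.6-0.9. 70% boys; 50% gives almost the same results.

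**The plan's own figure.** 2 × [1.7 × (2.241 + 1.282)]² / 1.0² = 71.7. With the t distribution, 73 per arm gives 90.0% power. 73 / 0.89 = 82.02, rounded up to 83, and 3 × 83 = 249. The sample size reproduces. Children per site: 249 / 30 = 8.3.

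**How the rule works at one site.** Take a site tally of LP 1, Mini-KIDS 1, SCBT 0.
- Next child to SCBT: counts (1,1,1), pairwise differences sum to 0.
- Next child to LP: counts (2,1,0), sum 1 + 2 + 1 = 4. Mini-KIDS gives the same.
- If the gender counts are level, gender adds the same amount for each arm. SCBT is therefore preferred and gets 0.8, the others 0.1 each.
- Uneven gender counts can sometimes blunt this, and the SLT does not see them trial-wide. The guess is therefore probabilistic.

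**Simulated predictability** (guess the least-used arm at the own site, ties broken at random):

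| Setting | All guesses right | Right when one arm alone is behind |
|---|---|---|
| Chance | 33% | 33% |
| Site + gender, weight 0.8 | 49% | 68% |
| Site + gender, weights 0.6-0.9 | 43-52% | 51-77% |
| Language region + gender | 34% | 34% |

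One arm alone is behind for about 38% of children. If imbalance is scored on proportions rather than raw counts, overall success is 50-57% for weights 0.7-0.9. Permuted blocks of 3 or 6 within site would be no better (54% overall, 82% when one arm is behind). The cause is balancing within site, not minimisation as such.

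**What selection could do.** SE = 1.7 × √(2/73) = 0.281. The chance of passing a program truly 1.0 %SS worse is Φ(bias/0.281 − 2.241). Suppose enrolled children differ by +0.5 %SS when LP is predicted and −0.5 %SS when LP is not among the least-used arms. At weight 0.8 the bias per unit of shift is 0.48.
- All 30 SLTs select against LP: bias 0.5 × 0.48 = 0.24. Φ(0.854 − 2.241) = 8%, against 1.25% nominal. For weights 0.6-0.9: bias 0.14-0.28, false non-inferiority 4-11%.
- All select, shift 0.3: bias 0.144, Φ(0.512 − 2.241) = 4%.
- A quarter of SLTs select against LP: bias about 0.05-0.07. At 0.07, Φ(0.249 − 2.241) = 2.3%.
- One third select each way: bias about 0.00, false non-inferiority 1.3%.
- All select in favour of LP: bias −0.24. For a truly equal program, power is Φ(0.76/0.281 − 2.241) = Φ(0.46), about 68%, instead of Φ(1.0/0.281 − 2.241) = Φ(1.32), about 90%.

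**Whether an analysis can detect it.** In the simulated worst case, adding site-tally terms for two arms cut the bias from 0.25 to about 0.01 %SS and false non-inferiority from 8% to about 1%. The standard error rose from 0.285 to 0.301 (0.301/0.285 = 1.06).

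**The case against.** **Direction.** A reader might infer that the scheme tilts the trial towards declaring non-inferiority. The documents do not support that. The focus-group remark and the SLT survey (Appendix 2) show that preferences may exist, not which way they run. Section 1 calls LP the option with the strongest evidence and describes different orientations among Dutch- and French-speaking therapists. Mixed preferences are at least as plausible as a shared one, and a preference for LP would work against non-inferiority. This part of the objection stands.

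**Size.** The ±0.5 %SS shift is a contrast of 1.0 %SS at enrolment. That equals the whole margin and is about 0.6 SD (1.0/1.7). Section 1 itself says that persistence cannot be predicted in the individual child. The 0.24 %SS and 8% also assume that every SLT selects at every informative enrolment and that nothing is adjusted for. They are a worst case. This stands too.

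**Room to act.** Active monitoring is tied to signs of recovery, and its dates are recorded. Waiting helps only if another child is randomised at the site meanwhile. At the 1.5 children per site per 3 months expected in 11.2, the longest delay allows one or two changes of tally. The one third of families expected not to take part reflects at least partly parental consent. The SLT's latitude is real but limited.

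**Why site is there.** Each SLT delivers all three programs, so balance within SLT is a legitimate aim. If site is replaced by language region, sites with an empty arm rise from about 0.5% to about 9%.

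What does not fall is the predictability. It needs no assumption about behaviour and exceeds chance at every weight tried.

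**Conclusion.** The point holds as an unaddressed predictability of allocation. An SLT who knows only the own-site history guesses the next arm correctly about 49% of the time, against 33% by chance, and 68% of the time when one arm alone is behind. These figures rest on an assumed weight of 0.8. The overall range of 43-52% covers weights of 0.6-0.9.

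The protocol shows an opportunity for selection. It does not show that selection occurred, and the direction of any bias is unknown. The bias of 0.24 %SS and the 8% false non-inferiority mark the upper end, where all SLTs select against LP and nothing is adjusted. Under partial or mixed selection the figures are about 0-0.07 %SS and 1-2%. Confidence is high in the predictability and moderate at most in any consequence for the result. A check is still worth pre-specifying, because it is cheap and the primary model now contains neither minimisation factor as a covariate.

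**What to change.** 1. **Sensitivity analysis (11.3.2/11.3.3).** Pre-specify a repeat of the primary comparison that adds, for two of the three arms, the arm's standing in the site tally just before the child's randomisation. The arm's allocation probability, reconstructed from the QMinim log, is an alternative. Report whether each non-inferiority conclusion still holds. Two terms are needed because there are three arms.
2. **Primary model (11.3.2).** Add the minimisation factors: SLT/site as a random intercept, and gender. This changes the primary analysis and should be fixed before database lock.

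Cost: no new data, since the allocation history is already stored. The standard error in the sensitivity analysis is about 6% larger with tally terms, and up to about 25% larger with full allocation probabilities at weight 0.8.

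**Optional, for children not yet randomised.** The sponsor may weigh a lower preferred-arm probability in QMinim, which helps only partly (43% of guesses are still right at 0.6), or language region in place of site (34%). The second makes arms less even within SLT: the mean gap between largest and smallest arm is about 2.7 children per site instead of 1.3, and about 9% of sites have an empty arm. Neither is a required correction.

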### **8.3.1 Method of implementing the allocation sequence**

A web-based randomisation system QMinim will be used.

If the screening is successfully completed and the informed consent is signed by the parent(s), the SLT at the site fills out a Request to randomisation in REDCap. This randomisation form contains the unique enrolment ID from REDCap, year of birth and gender. Thereafter REDCap generates an automatic email to a staff member from CTC UZ-Antwerpen about the request including only the unique enrolment ID from REDCap. The staff member will fill in the values for the site and gender in QMinim in order to randomize the PCWS. The allocated treatment program and allocation ID (from QMinim) are filled in by the randomizer in REDCap. The allocation is performed in chronological order (based on the timing of the automatic emails from REDCap). The requests for randomisation are answered within 24 hours on weekdays (9 am-5 pm). The PCWS can start treatment the next day.

There is no need to have access to randomisation codes in case of an emergency as the study is open label. Hence, treatment will be known by the PCWS as well as SLT and recorded in the PCWS's speech-language therapy file and the electronic Case Report Form (eCRF) (REDCap).

